#### Procedure

In each hospital, four *professionals will be taught in a train-the-trainer seminar* to train patients and their social support providers based on the short manual developed to teach communication competences. Recruitment will take place via the doctors, nurses and midwives in the hospitals (Fig. 5 in Appendix). The quality management departments will be involved to ensure adequate enrollment in order to reach the target sample size of N = 423 participants. Informed consent will be collected by on-site project managers. When an expectant mother is admitted to the clinic and agrees to participate in the study, she will be randomly assigned to a training group (IG) or a control group (CG). If she is accompanied by a partner, relative, or close friend, they will be assigned to the same group. All patients and social support providers randomly assigned to the intervention group will receive the same training content over the course of this study. In contrast, the control group will receive the hospital care-as-usual (see Fig. 5 in Appendix).

*Randomization* will be done per site and day (block randomization). The central project coordinator will generate the allocation sequence. Depending on this sequence, all patients admitted to the hospital on that day will be allocated to either the IG or to the CG. Patients and staff will not be informed beforehand on which days allocation to the IG or the CG takes place to prevent biases. Instead, the on-site project manager at each hospital will receive a sealed envelope each day containing this information, enabling them to inform other staff involved as well as enroll and assign participants to the CG or IG treatment. This process allows trial participants, general care providers, outcome assessors and data analysts to remain blinded throughout the allocation sequence. Trial participants and general care providers will be unblinded in case they ask for more information about the training. Revealing a participant’s allocated intervention during the trial can be performed after completion of the IG treatment to disclose the content of the intervention. A flyer will be provided containing this information, which will be also used after the study to disseminate findings and tools. Inclusion and exclusion criteria are outlined in Table 6.

**Table 6 Tab6:** Summary of the inclusion and exclusion criteria

*Inclusion criteria*	*Exclusion criteria*

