Expectant mother or *patient* in gynecology and obstetrics or *social support providers* (spouse/partner, relative, close friend) to be recipient of the training *Professional* in a gynecology and obstetrics hospital to be trainer of the patients and the social support providers	Not proficient in the German language and/or does not have the capability of writing Severe cognitive deficits (unable to read/write/answer questions) and impairments due to diagnosed brain injuries, neurological disorders, etc. Insufficient corrected eyesight (patients must be able to read on the cell phone) Participation in another research study or intervention trial conducted in the clinic
Aged 18 years and above	Younger than 18 years
Healthy volunteers	High risk, emergency case
Declaration of consent for participation in the study	Withdraw of consent for participation in the study at any point in time

According to a power analysis, a sample of *N* = 352 is necessary (alpha error = 0.05, power = 80%, to be analyzed IG _analysis_: *N* = 176; CG _analysis_: *N* = 176) in order to detect an effect size of *d* = 0.3. With an assumed drop-out rate of 20%, *N* = 423 participants (IG _recruited_: *N* = 212; CG _recruited_: *N* = 211) have to be recruited in the study. The pAEs will be collected on an individual basis (anonymized) and coded according to the communication competences (see Fig. 5 in Appendix).

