#### Statistical analyses

To test the effectiveness of the digital app, a case-control study will be performed (see Fig. 6 in Appendix). Cases are newly recruited individuals that fulfil the inclusion criteria outlined in Table 6. Comparators/controls are the participants in one of the two intervention arms of the previously conducted RCT study in Phase 2 (i.e. patients; historical control groups; No-Treatment CG _analysis_: *N* = 176; No-Treatment CG _recruited_: *N* = 212; Previously Treated/Active CG _analysis_: *N* = 176 (called IG1 in Fig. 6 in Appendix); Previously Treated/Active CG _recruited_: *N* = 212, see in section Phase 2). *N* = 176 participants need to be analyzed for the intervention group (IG2 _analysis_). Assuming a drop-out of 20%, *N* = 212 participants have to be recruited for the intervention group (IG2 _recruited_) in Phase 3 (see Fig. 6 in Appendix). The intervention will also be provided to the professionals in the clinic. Adoption and acceptance of the intervention will be evaluated in all groups by means of observational data and self-report. Target criteria are specified in Tables 1 and 2.

At the end of Phase 3, the results from all three phases will be disseminated using a white paper with recommendations for practice. Further plans to communicate trial results to participants, healthcare professionals, the public, and other relevant groups via publication, presentations and press releases will be developed using a participatory approach, with the restriction that anonymity is ensured at all times.

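### The 20% drop-out allowance multiplies by 1.2 instead of dividing by 0.8, so 423 recruits (212 per group) are not expected to leave the 352 (176 per group) stated as necessary

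*Protocol article*

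**What the plan says.** Protocol article, Methods/design, Phase 2, Procedure (paragraph after Table 6). The sample size is set with "alpha error = 0.05, power = 80"%, "in order to detect an effect size of *d* = 0.3". The number needed is 352, split as "to be analyzed IG _analysis_: *N* = 176; CG _analysis_: *N* = 176". The next sentence moves from analysed to recruited numbers: "With an assumed drop-out rate of 20%, *N* = 423 participants (IG _recruited_: *N* = 212; CG _recruited_: *N* = 211".

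Earlier in the same Procedure section 423 is the operational target: quality management departments are to be involved so that the sites "reach the target sample size of N = 423 participants".

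Phase 3, Statistical analyses, uses the same allowance for the app group (IG2), where 176 are to be analysed: "Assuming a drop-out of 20%, *N* = 212 participants have to be recruited for the intervention group". That paragraph also lists the two Phase 2 arms, reused as historical controls, as 176 analysed from 212 recruited each.

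**The concern.** The protocol prints three linked figures: a number required in the analysis, a drop-out rate, and a number to recruit. Any two determine the third, and these three do not agree. A drop-out rate is a share of those recruited, so the required number has to be divided by the proportion retained. Adding 20% of the analysed number to itself gives too few recruits.

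What is at stake is internal consistency. The sites could meet the recruitment target, drop-out could run exactly as assumed, and the analysis would still fall short of the number the protocol calls necessary. The slip carries into Phase 3, which applies the same multiplier to the app group and takes both Phase 2 arms as comparators.

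**Working it through.** **Inputs** (Phase 2, Procedure, and Phase 3, Statistical analyses): alpha 0.05, power 80%, d = 0.3, 1:1 allocation, drop-out 20%; 352 analysed and 423 recruited (212 + 211) in Phase 2; 176 analysed and 212 recruited for IG2. Sidedness is not stated; the check below settles it.

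**1. Analysed number.** A two-sample t-test, two-sided alpha 0.05, 80% power, d = 0.3, gives n = 175.4, so 176 per group and 352 in total. This matches exactly; power at 176 per group is 80.1%. A one-sided test would need about 138 to 139 per group, so the plan's figure is two-sided.

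**2. Recruited number.** Two candidate formulas:

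| Step | Analysed × (1 + 0.20) | Analysed / (1 − 0.20) | Printed |
|---|---|---|---|
| Phase 2 total | 352 × 1.2 = 422.4, so 423 | 352 / 0.8 = 440 | 423 |
| Per group, and IG2 | 176 × 1.2 = 211.2, so 212 | 176 / 0.8 = 220 | 212 (211 for the Phase 2 control group) |

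The printed totals follow the first formula. The second is the one that a drop-out rate of 20% requires.

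**3. What the printed recruitment is expected to leave at 20% drop-out.**
- Phase 2 total: 423 × 0.8 = 338.4, about 338, which is 352 − 338 = 14 short.
- Phase 2 groups: 212 × 0.8 = 169.6, about 170; 211 × 0.8 = 168.8, about 169.
- Phase 3 IG2: 212 × 0.8 = 169.6, about 170, which is 6 short of 176. The same holds for each historical control group when it is taken as 212 recruited, as Phase 3 lists it.

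**4. Drop-out that 423 can absorb.** 1 − 352/423 = 0.168, about 16.8%.

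**5. Effect on power** (same two-sided t-test, unadjusted, independent individuals, d = 0.3):

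| Analysed per group | Power |
|---|---|
| 176 / 176 | 80.1% |
| 170 / 169 | 78.6% |

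The loss is 80.1 − 78.6 = 1.5 percentage points. The effect detectable with 80% power at 170 / 169 is about d = 0.305.

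**The case against.** The strongest counter-argument is that power in the planned analysis need not fall below 80%. The analysis is not an unadjusted comparison. Phase 1, Statistical analyses, takes baseline values as covariates; Phase 2 follows it and adds ANCOVAs; Table 2 shows communication competences measured at T1 and T2. The article gives no baseline–outcome correlation, so the following is an assumed range. With effective effect size d / √(1 − r²) and 169 per group:

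| Assumed r | Effective d | Power |
|---|---|---|
| 0.2 | 0.306 | 80.1% |
| 0.3 | 0.314 | 82.2% |
| 0.5 | 0.346 | 88.8% |

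Full information maximum likelihood, planned for all phases, may also recover information from people who drop out.

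This stands as far as it goes. A reader might infer from the slip that the trial loses its 80% power in the analysis it will run, and the documents do not support that. Neither do they support the reverse: allocation by site and day and the inclusion of dyads could lower power, and the power statement mentions neither. The 78.6% therefore describes only the simple comparison behind the plan's own 352.

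None of this reconciles the printed figures. The protocol itself separates analysed from recruited participants, treats drop-out as the difference, and calls 352 necessary after drop-out.

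A reader might also infer that 423 recruits could never yield 352. That is too strong: they do if drop-out is about 16.8% or less. The shortfall is what is expected at the assumed 20%.

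**Conclusion.** The recruitment figures are wrong as written, in Phase 2 and again in Phase 3, because the allowance multiplies by 1.2 instead of dividing by 0.8. The shortfall is 17 recruits against 440 in Phase 2 and 8 against 220 in the app group.

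This is a minor arithmetic correction and not a serious loss of power. The stated size of the loss assumes a two-sided two-sample t-test at d = 0.3, independent individuals, exactly 20% drop-out, and no baseline adjustment. No hypothesis or analysis method changes. The 176 per group is a correct requirement under the stated inputs; the fault lies only in the step from analysed to recruited numbers.

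**What to change.** Make the three figures agree, in one of these ways:

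- **Keep 423 and 212, and change the allowance.** State a drop-out allowance of about 16.8% in Phase 2 and correspondingly in Phase 3. The 352 and 176 analysed then stand. Cost: wording only.
- **Keep 423, 212 and 20%, and change the analysed numbers.** State about 338 analysed in Phase 2 (about 170 and 169 per group), about 170 per group in Phase 3, and power of about 78.6% for d = 0.3. Say that this power is for the unadjusted individual-level comparison, before baseline adjustment, allocation by site and day, or dyads. The Phase 3 analysed entries change too. Cost: wording only.
- **Keep 352, 176 and 20%, and change recruitment.** State 440 in Phase 2 (220 per group) and 220 for IG2. The analysed entries stay, and only the recruited numbers change wherever they appear, including the site target in Phase 2, Procedure, and the Abstract. Cost: 440 − 423 = 17 more recruits in Phase 2 and 220 − 212 = 8 more in Phase 3.

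While editing, align the recruited number for the Phase 2 control group, given as 211 in Phase 2 and 212 in Phase 3.

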#### Statistical analyses

The target criteria (see Tables 1 and 2) will be evaluated statistically and clinically, as in Phase 1, with linear and general mixed models and with *superiority trial tests* to investigate whether the intervention is better than the standard care. As expecting mothers and their social support providers participate in the intervention, dyadic data will be assessed and analyzed. Additional analyses will test whether subgroups of patients with psychological risk factors (e.g., depressive symptoms, anxiety) and low motivation benefit from the intervention to the same extent as study participants without such risk factors. Furthermore, adjusted analyses will be performed in terms of ANCOVAs considering factors related to social inequality, such as education, anxiety, and immigration status (see also Table 2).

### Phase 3: implementation of the app and case-control study

#### Functions of the app

A digital app will be developed to help users communicate well. The app will be developed in a participatory and theory-driven way from all findings and conclusions obtained in Phases 1 and 2 (Fig. 2) [66]. Stages D and E of Phase 1 will be repeated with professionals, expecting mothers/patients, and social support providers to update the evidence and answer questions that may have arisen during Phase 2. The aim of Phase 3 is to determine exactly how the app can support communication between professionals, patients, and their social support providers in their daily work/hospital experience and thereby lead to a reduction in pAEs. As app users will have completed the face-to-face training, they can use the app at their convenience to monitor their behavior and experiences (see Fig. 3) and deepen their skills and knowledge. To achieve this aim, there will be two functions of the app.

**Fig. 3 Fig3:**
[figure not shown]
Example of the monitoring and guidance functions of the app

Firstly, the app will be designed to provide guidance on how to cope with specific (future) communication problems including communication initiated by a) the patient, b) the professional and c) between professionals. The following scenarios illustrate how the app may improve communication. Regarding a), if a woman prepares for a conversation with a professional in a labor ward, she may worry about how to express the wish for peridural anesthesia or more anesthesia if the pain escalates (cf. [21]). The app explains/provides suggestions to her (and her social support providers) how to communicate this wish in a clear and constructive way [43, 51] (Fig. 3). This may enable *shared decision making* in terms of understanding risks and disadvantages. Furthermore, she is supported to ask the right questions or maybe even audio record her questions and the answers from professionals, as it has been done in previous research [49]. Regarding b), a doctor may be unsure how to handle the expectant mother’s fear of childbirth and postpartum posttraumatic stress disorder (cf. [67]). Typical problems include sharing bad news and dealing with difficult emotions [24, 68, 69]. The app would help the doctor to communicate accurate information in a way that still addresses the fear that may come along with bad news. This may prevent complications due to insufficient information. Professionals will be asked to analyze and solve scenarios that involve both patients and their social support providers. The app will then explain the communication competences again and give concrete suggestions how to use them for solving the case. Depending on demands, the app will give suggestions such as “Speak slowly”, “Try not to use acronyms or abbreviations”, “Try to refrain from using scientific terms”, “Make use of visualizations”, “Be sensitive to verbal and non-verbal cues that may indicate lack of understanding”, “Stress the most important aspects that the patient must keep in mind”, and “Make use of the teach-back method” [19]. Regarding c), one team member of the delivery ward knows that a high-risk patient in labor needs prophylactic negative-pressure wound therapy (NPWT) after cesarean delivery, but they do not know how to communicate this to colleagues under time pressure [20]. The app helps to overcome time pressure by providing a message on the display for the colleagues which can be copied to a piece of paper, and thus support communication [70]. All of the above cases will be provided to colleagues, who will be asked to analyze and solve them. Communication competences will be explained with regard to communication between colleagues. Depending on demands, specific suggestions such as communication tools (daily goal sheet, bedside whiteboard, or door communication card), trust building, mindfulness, and reflective exercises will be given [71].

Secondly, the app will assist in monitoring typical or recent communication with focus on (1.) one’s own role, (2.) the role of the communication partner and (3.) resonance (a feeling of mutual understanding), thus supporting the development of general communication competences. These aspects will be evaluated with regard to the communication competences (see Tables 1 and 2).

Learning from the communication of all participants is ensured by collecting dyadic self-reported data and the partners reported data. Concretely, target-group specific tasks that train general communication competences seldom aid to overcoming specific obstacles, so reminders of resources and application/transfer options will be provided in the app, too.

#### Procedure, sample and data collection

Patients will be recruited via doctors and midwives in the hospitals; recruitment of staff and collection of informed consent of both patients and staff will be conducted by the on-site project managers. Quality management departments will be involved to ensure adequate participant enrollment to reach the target sample size. The target criteria of the patient sample will be evaluated statistically and clinically as in Phase 1 and 2 (see Table 2). Group differences will be tested with linear and general mixed models and with *superiority trial tests* that investigate whether the intervention is helping more than the standard care in Phase 2.

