**Methods:**

The study will take place in two maternity clinics in Germany. In line with previous studies of complex interventions, it is divided into three interdependent phases. Each phase provides its own methods and data. Phase 1: Needs assessment and a training for staff (*n* = 140) tested in a pre-experimental study with a pre/post-design. Phase 2: Assessment of communication training for patients and their social support providers (*n* = 423) in a randomized controlled study. Phase 3: Assessment of an app supporting the communication between staff, patients, and their social support providers (*n* = 423) in a case-control study. The primary outcome is improvement of communication competencies. A range of other implementation outcomes will also be assessed (i.e. pAEs, patient/treatment satisfaction, work satisfaction, safety culture, training-related outcomes).

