This will be scientifically evaluated using a three-phase study, in which phases are built sequentially on each other and described in detail in the method section: Phase 1, *implementation phase* (including needs assessment, retrospective cohort study of pAEs) *and pre-experimental study* with a group and pre−/post-test testing the effect of a training for professionals; Phase 2, *quasi-experimental efficacy study* with a randomized controlled trial study design (RCT) testing the effect of a training addressing patients and their social support providers; Phase 3, implementation of the app, aimed at staff, patients, and their social support providers, which will test the effect in *a case-control study*. Efficacy indicators are outlined in Table 1.

The *hypotheses* are the following: for Phase 1, it is expected that as a result of the training (1.) the communication competences of healthcare providers will measurably improve. As a result, (2.) healthcare providers will be more satisfied (3.) and the number and severity of pAEs should be significantly reduced for short and medium term (i.e. over the period of the intervention study and beyond). In Phase 2, it is expected that patients and their social support providers in the intervention group will develop significantly (4.) higher competences in communication with staff as well as (5.) higher satisfaction after the intervention compared to patients and their social support providers in the control group. It is also expected that (6.) the number and severity of pAEs in the intervention group will be significantly reduced compared to the number and severity of pAEs in the control group. For Phase 3, we hypothesize that the intervention group using the app compared to the intervention group without the app will show (7.) higher patient and healthcare provider communication competences and (8.) satisfaction as well as (9.) a significant reduction in the number and severity of pAEs. The effects of the training on communication competences may be (10.) mediated by training-related and personal outcomes and moderated by organizational factors (11.). All interventions in all phases will improve organizational outcomes if communication competences are improved successfully. Thus, the hypotheses will be tested in this project.

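### Phase 3 does not fix its comparator: the hypotheses contrast training plus app with training alone, but the superiority test is stated against Phase 2 standard care

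*Protocol article*

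**What the plan says.** Five places in the protocol article bear on the Phase 3 contrast.

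- **Research questions and hypotheses.** For hypotheses 7 to 9, "the intervention group using the app compared to the intervention group without the app will show" better communication competences and satisfaction and fewer or less severe pAEs.
- **Phase 3, Procedure, sample and data collection.** Group differences are to be tested with mixed models and with superiority tests that "investigate whether the intervention is helping more than the standard care in Phase 2".
- **Phase 3, Statistical analyses.** The stated purpose is to test the app's effectiveness. "Comparators/controls are the participants in one of the two intervention arms of the previously conducted RCT study in Phase 2". The same sentence then lists two historical groups, each with 176 to be analysed: a no-treatment control group and a previously treated, active control group (IG1). The section adds: "The intervention will also be provided to the professionals in the clinic".
- **Phase 3, Functions of the app.** "As app users will have completed the face-to-face training", they use the app in addition to that training.
- **Phase 2, Procedure.** The control group receives the hospital's usual care, so standard care in Phase 2 means the untrained arm. The Phase 2 analysis section uses the term in the same sense.

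The article calls Phase 3 a case-control study throughout. The abstract gives its size as 423.

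**The concern.** The hypothesis and the stated superiority test are different contrasts. IG2 versus IG1 asks what the app adds to training. IG2 versus CG asks what the whole package achieves over no training. The analysis section does not settle the matter: it speaks of one of the two Phase 2 arms, names both, and assigns neither to hypotheses 7 to 9. An analysis plan that follows one section would depart from another.

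The choice matters for the conclusion. A difference from standard care could come entirely from the training, yet the section that reports it is introduced as the test of the app. The results are to feed a white paper with recommendations for practice, and the Discussion presents digital training as a way round time-consuming face-to-face sessions. A package effect read as an app effect could support dropping the component that worked.

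The design label adds to the difficulty. Groups are formed by exposure to the app and by period, not by outcome, so this is not a case-control study. It is a non-randomised comparison with non-concurrent controls.

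**Working it through.** **1. Inputs.** From the Phase 2 Procedure section: alpha 0.05, power 80%, 176 analysed per arm, chosen "in order to detect an effect size of *d* = 0.3". The article does not say whether the test is one-sided or two-sided. No separate effect size is given for Phase 3, which reuses 176 per group.

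**2. Reproducing the plan's figure.** For a two-sided test,

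n per arm = 2 × (1.960 + 0.842)² / d² = 2 × 7.849 / 0.09 = 174.4, so 175.

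The t-test version gives 175.4, so 176 per arm and 352 in total, as stated. A one-sided test gives 138 and does not match, so two-sided 0.05 is used below.

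**3. What each contrast estimates.**

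- IG2 versus CG: training + app + app provision to staff + calendar time.
- IG2 versus IG1: app + app provision to staff + calendar time. The training cancels; the period difference does not.

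**4. Probability of a significant result at 176 per arm.** Power = Φ(d × √(176/2) − 1.960) = Φ(9.381 × d − 1.960).

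| True difference d | 9.381 × d − 1.960 | Probability |
|---|---|---|
| 0.1 | −1.022 | 15% |
| 0.2 | −0.084 | 47% |
| 0.3 | 0.854 | 80% |
| 0.4 | 1.792 | 96% |

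Only 0.3 is the protocol's value; the other rows are assumptions.

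**5. Reading the table for IG2 versus CG with no app effect.** The true difference is then the training effect alone, leaving aside any staff or period effect. At the planned d = 0.3 the test is significant about 80% of the time. Against IG1 the corresponding rate is the nominal 5%, before any period effect.

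**6. Reading the same table for IG2 versus IG1.** The true difference is now the app's own increment. Power is 80% if the increment is 0.3, 47% if it is 0.2 and 15% if it is 0.1. Restoring 80% would need 2 × 7.849 / 0.04 = 392.4, so 393 per arm, at 0.2, and 1,570 per arm at 0.1.

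**7. Sample size in the abstract.** 212 new app participants + 211 (the control arm as recruited in the Phase 2 Procedure section) = 423, so the abstract fits one two-group comparison. The Phase 3 analysis section gives 212 for the same control arm, hence 212 + 212 = 424, or 3 × 212 = 636 with both historical groups.

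**The case against.** A reader might infer that Phase 3 plans no comparison with the trained arm and will credit the training effect to the app. The documents do not support that. The Phase 3 analysis section names IG1 as a historical control with its own numbers, the hypotheses state the right contrast, and nothing excludes IG2 versus IG1 from the mixed models. The standard-care clause attaches most naturally to the superiority tests alone. The flow figure for Phase 3 is not shown, and a fuller German protocol exists; either may rank the contrasts. All of this stands, and it makes the fault one of reconciliation, not of a missing comparator.

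The 80% is also conditional. It is the Phase 2 design power carried over, and a significant IG2 versus CG result would be a correct finding about the package. It misleads only if attributed to the app.

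A reader might also infer that the abstract's 423 contradicts the Phase 3 text. It does not clearly do so, since 212 + 211 = 423. What remains is that the abstract does not say the controls are reused, and that the control arm is 211 in one place and 212 in another.

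Finally, the case-control label is wrong, but the article openly says that the app group is newly recruited and the controls are historical. The label hides nothing and does not itself claim randomised strength. Correcting it is secondary.

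What the objection does not remove is the mismatch between the hypotheses and the stated superiority test.

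**Conclusion.** The point holds as an unreconciled comparator. The hypotheses require IG2 versus IG1, the superiority test is worded against the untrained arm, and the analysis section lists both without assigning either. Because app users are also trained, the standard-care contrast cannot isolate the app.

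The size depends on two conditions: that the standard-care test is taken as the test of the app, and that the app adds nothing. The chance of a significant result is then about 80% at the planned training effect of d = 0.3, and ranges from 15% to 96% over assumed training effects of 0.1 to 0.4. These figures take two-sided 0.05, 176 analysed per arm and no period or staff effect.

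The design label needs correcting alongside this. The numbers in the abstract are an editorial matter only.

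**What to change.** 1. In the Phase 3 procedure and analysis sections, name IG2 versus IG1 as the test of hypotheses 7 to 9. Use the baseline, clinic and covariate adjustment already planned for Phases 1 and 2. Keep IG2 versus CG as a secondary comparison of the package with usual care.
2. State that 176 per arm gives 80% power only if the app's own increment over training is d = 0.3, and about 47% at an assumed 0.2.
3. Describe Phase 3 as a non-randomised comparison with non-concurrent (historical) controls, and limit its conclusion to association. Covariate adjustment will not remove period effects.
4. Editorially, say in the abstract that 212 participants are newly recruited and that the controls are reused from Phase 2. Reconcile 211 with 212 for the recruited control arm.

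These are changes of wording and analysis and need no new data. The cost is a more modest Phase 3 claim, and lower power for the main contrast if the app adds less than 0.3.
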